### Statistical analyses

Data will be analyzed based on the intention-to-treat principle. We will use a multilevel generalized linear model for count data to assess the effectiveness of HypoAware on the frequency of severe hypoglycaemia, while allowing for clustering of events in patients and clinics. Secondary outcomes will also be assessed using multilevel (generalized) linear models in case of continuous, count or ordinal outcome variables. Generalized Estimation Equations (GEE) will be used to analyse dichotomous outcome variables.

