### Randomisation

Cluster randomisation will be done prior to recruitment of participants at the level of the participating clinics to avoid contamination within the clinics. The participants in the control group receive the intervention after the 6 months follow-up as an incentive to participate. Random allocation will be performed by two members of the study team, who randomly select notes from two opaque envelopes, one with the eight names of the clinics and one with four notes with ‘intervention’ and four notes with ‘control’. Participants will be allocated based on the clinic where they are registered.

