### Sample size

A power analysis was performed to determine the sample size using STATA 11.2 (Statacorp, Texas, USA). We based our effect size on a randomised controlled trial of the intervention BGAT that showed the most conservative effect [16]. Mean frequency of severe hypoglycaemia at baseline was 1.61 (SD 3.49) and 0.13 (SD 0.33) 6 months post BGAT. The control condition (group education about diabetes guided by a physician) scored 1.76 (SD 3.71) at baseline and 1.07 (SD 2.85) after 6 months. This implicated that, with 3 follow-up measurements and ρ = 0.6, the alpha set at 0.05, a power of 80 %, and adjusting for clustering within 8 diabetes teams with an ICC of 0.01 as described by Twisk [17], we need 62 patients per group (total *n* = 124) to perform our primary analyses. Anticipating a 20 % loss to follow-up, we aim to randomise 77 patients per group (total *n* = 154).

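### The sample size ignores the 6 between-clinic degrees of freedom: a test that respects eight clinics has about 65 to 73% power, not 80%, and large-sample tests would instead exceed 5%, mainly under GEE

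*Protocol article*

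**What the plan says.** All references are to the protocol article.

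- **Randomisation.** Allocation is by clinic, drawn from two envelopes: "one with the eight names of the clinics and one with four notes with ‘intervention’ and four notes with ‘control". There are therefore four clinics per arm.
- **Sample size.** The 6-month results of an earlier trial supply the effect: "0.13 (SD 0.33) 6 months post BGAT" against "1.07 (SD 2.85) after 6 months" in the control arm. The calculation is run "with 3 follow-up measurements and ρ = 0.6", with "the alpha set at 0.05, a power of 80" per cent, and "adjusting for clustering within 8 diabetes teams with an ICC of 0.01". The result is 62 per group (124 in total), raised to 77 per group (154 in total) for 20% loss.
- **Statistical analyses.** The primary count outcome gets a multilevel generalised linear model "while allowing for clustering of events in patients and clinics". Continuous, count and ordinal secondary outcomes also get multilevel models. For the rest, "Generalized Estimation Equations (GEE) will be used to analyse dichotomous outcome variables". The section names no reference distribution, degrees-of-freedom method or sandwich correction.

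**The concern.** When whole clinics are randomised, evidence about the treatment effect comes from variation between clinics. Eight clinics less two arm means leave 6 degrees of freedom, for which the two-sided 5% critical value is 2.447 rather than 1.960. A design effect inflates the variance for clustering, but it does not allow for how poorly that variance is estimated from eight clinics.

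The cost falls in one of two places. A test that uses the 6 df has less power than stated. A test that ignores them rejects a true null too often. GEE needs extra care because a standard GEE has one cluster level, while these data have repeated measures within patients and patients within clinics. Clustered on clinic, the usual sandwich variance from eight clusters is biased downwards. Clustered on patient, it leaves out the unit of randomisation.

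The Discussion ties a favourable result to national adoption, so both a missed effect and a false positive would matter.

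**Working it through.** **Inputs (Sample size and Randomisation).** Means 0.13 and 1.07, difference 0.94; SDs 0.33 and 2.85; three follow-ups with ρ = 0.6; ICC 0.01; four clinics per arm; alpha 0.05, taken as two-sided because that reproduces the stated number.

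**1. The plan's own figure.**
- Simple comparison of means: (1.960 + 0.842)² × (0.33² + 2.85²) / 0.94² = 73.1 per arm.
- Repeated measures: factor (1 + 2 × 0.6) / 3 = 0.733, giving 53.6.
- Clustering: 62 / 4 = 15.5 patients per clinic; design effect 1 + 14.5 × 0.01 = 1.145, giving 61.4, rounded up to 62.
- Loss: 62 / 0.8 = 77.5, stated as 77. This rounding is immaterial.

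The 62 is reproduced, and only with normal quantiles.

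**2. Power on 6 df, same inputs.** The standard error is √[(0.33² + 2.85²) × 0.733 × design effect / n], and the noncentrality is 0.94 divided by it.

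| Evaluable per arm | Design effect | Noncentrality | Power, normal | Power, t on 6 df |
|---|---|---|---|---|
| 62 | 1.145 | 2.815 | 80.4% | 65.3% |
| 77 | 1.1825 | 3.087 | 87.0% | 73.1% |

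Reaching 80% on 6 df with four clinics per arm takes about 96 evaluable per arm (96 / 0.8 = 120 recruited). The ICC of 0.01 is itself an assumption. At 62 per arm, power on 6 df is 56% for an ICC of 0.03 and 49% for 0.05.

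**3. Type I error with large-sample references.** This part needs assumptions beyond the document: a Wald test against 1.96, and for GEE an uncorrected sandwich and a choice of cluster level.

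*Multilevel model.* The check is a linear analogue, not the planned count model: simulated 4 v 4 clinics, 16 patients each.

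| ICC | REML, 1.96 | ML, 1.96 |
|---|---|---|
| 0.01 | 4.9% | 6.1% |
| 0.05 | 7.3% | 9.6% |
| 0.10 | 8.6% | 12.2% |

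At ICC 0.01 and noncentrality 2.8, the same uncorrected tests have power of 76% (REML) and 81% (ML).

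*GEE clustered on clinic.* With four equal clinics per arm, the uncorrected sandwich has expectation about 3/4 of the true variance. Comparing with 1.96 is then like comparing a t on 6 df with 1.96 × √0.75 = 1.697, which has a two-sided tail of 14%. Simulated beta-binomial data gave 13 to 14% at every ICC tried from 0 to 0.10.

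*GEE clustered on patient.* The standard error is too small by the square root of the design effect. With 15.5 to 19.25 patients per clinic:
- ICC 0.01: design effect 1.145 to 1.1825; 1.96 / √(design effect) = 1.83 to 1.80; two-sided normal tail 6.7 to 7.1%.
- ICC 0.05: design effect 1.725 to 1.9125; cut-off 1.49 to 1.42; tail 13.6 to 15.6%.

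Simulations agree: about 7% at ICC 0.01 and 14 to 17% at ICC 0.05.

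**The case against.** The strongest reply is that half of this rests on silence. The article gives its analysis one paragraph, the primary model has the right structure with patients and clinics both as levels, and the reference distribution and variance estimator are details that a statistical analysis plan usually supplies. That stands. A reader might infer that the plan has chosen uncorrected tests, but the text does not say so, and the figures in step 3 are conditional.

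A reader might also infer that power is 65% and type I error is inflated at the same time. For any one test these are alternatives: the lower power belongs to a test on 6 df, the inflation to a test that ignores them.

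Nor does the document support a claim that the primary analysis is badly inflated. At the planned ICC the linear analogue runs at about 5 to 6%. The larger GEE figures concern dichotomous variables, and the Outcomes section names none: it lists event frequencies, questionnaire scores and clinical data. GEE is not unusable here either, since a bias-corrected version clustered on clinic would serve.

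Finally, 65% is not the power of the planned count model. It is a normal approximation for means that credits only 62 per arm, whereas a multilevel model can use partial follow-up from the 77 recruited. That is why a range of 65 to 73% is fairer.

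What survives is the sample size, which is set out in the article and makes no allowance for 6 df whatever an analysis plan adds. The choice of GEE for data with two levels of clustering also survives, because the article states it outright.

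**Conclusion.** The concern holds in a limited form and should be fixed. The Sample size section states 80% power, but a test that respects the eight randomised clinics has about 65% at 62 evaluable per arm and about 73% if all 77 were evaluable. This takes the plan's means, SDs, ρ and ICC as given, uses a normal approximation for the means, and refers the test to t on 6 df.

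If large-sample references are used instead, power stays nearer 80% and the error moves to the type I side. For the primary model it is about 5 to 6% at ICC 0.01 and 7 to 10% at ICC 0.05 (linear analogue). For a dichotomous secondary outcome under standard GEE it is about 13 to 14% clustered on clinic, and about 7% (ICC 0.01) to 14 to 17% (ICC 0.05) clustered on patient.

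The main defect is the stated power. The type I error part is a smaller, conditional point.

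**What to change.** - **Sample size.** Restate the power on 6 df, as about 65 to 73% under the plan's inputs, and say that it depends on an ICC of 0.01.
- **Multilevel models.** Test the treatment term on about 6 df (between-within or Satterthwaite type). For the primary outcome, add a permutation check over the C(8,4) = 70 possible allocations; its smallest two-sided p-value is 2 / 70 = 0.029, so it can reach 5%.
- **Dichotomous outcomes.** Use a three-level logistic model with the same 6-df reference, or GEE clustered on clinic with a bias-corrected sandwich (Kauermann-Carroll or Fay-Graubard) and t on 6 df.

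The cost is some wording and a few lines of code, with wider intervals and a lower stated power. A fixed 6-df reference can also be conservative when the clinic variance is estimated at or near zero: in the linear analogue at ICC 0.01 it rejected about 2% of true nulls, with power of 59% (REML) to 66% (ML). Data collection is already under way, so the choice should be recorded before outcomes are compared by arm.

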#### Economic evaluation

Both a cost-effectiveness and cost-utility analysis will be performed with a time horizon of 6 months. Therefore, discounting is not necessary.

Societal costs will be related to the following effect measures in the economic evaluation: 1) Frequency of severe hypoglycaemia; 2) Quality-adjusted life-years (QALYs), calculated using the area-under-the-curve method with linear interpolation between time points. QALYs will be based on the Dutch tariff for the EQ-5D-5 L.

The analysis will be done according to the intention-to-treat principle. Missing cost and effect data will be imputed using multiple imputation techniques. Adjustment for confounders and effect modifiers will be done, if necessary. Sensitivity analyses will be performed to assess the robustness of the results using different assumptions regarding costs.

Incremental cost-effectiveness ratios (ICERs) will be calculated by dividing the difference in mean total costs between the HypoAware and usual care groups by the difference in mean effects. Bootstrapping with 5000 replications will be used to estimate 95 % confidence intervals around cost differences and the uncertainty surrounding the ICERs. Uncertainty will be graphically presented on cost-effectiveness planes. Cost-effectiveness acceptability curves showing the probability that the intervention is cost-effective in comparison with usual care for a range of different ceiling ratios will also be estimated.

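### The economic evaluation carries no clinic level into its cost and effect differences, imputation or bootstrap, although clinics are randomised and the sample size and clinical model both allow for them

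*Protocol article*

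**What the plan says.** All of this is in the Protocol article.

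- **Randomisation.** "Cluster randomisation will be done prior to recruitment of participants at the level of the participating clinics to avoid contamination within the clinics". The draw uses two envelopes, "one with the eight names of the clinics and one with four notes with ‘intervention’ and four notes with ‘control", so there are four clinics per arm.
- **Sample size.** The calculation works "with 3 follow-up measurements and ρ = 0.6, the alpha set at 0.05, a power of 80" per cent, "adjusting for clustering within 8 diabetes teams with an ICC of 0.01".
- **Statistical analyses.** Severe hypoglycaemia is analysed with a multilevel count model, "while allowing for clustering of events in patients and clinics". Continuous, count and ordinal secondary outcomes also get multilevel models.
- **Economic evaluation.** ICERs are obtained by "dividing the difference in mean total costs between the HypoAware and usual care groups by the difference in mean effects". On uncertainty: "Bootstrapping with 5000 replications will be used to estimate 95 % confidence intervals around cost differences and the uncertainty surrounding the ICERs". Missing costs and effects are multiply imputed, and confounders and effect modifiers are adjusted for if that proves necessary. Clinic is not mentioned in the estimator, the imputation or the bootstrap.

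**The concern.** Clinic is the unit of randomisation, so between-clinic variation belongs in the uncertainty of every comparison between arms. The article applies this to the clinical outcomes and then describes an economic analysis of the same eight clinics without it.

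The article also gives reasons to expect costs to cluster. Usual care is whatever each diabetes team normally provides (Control-care as usual). HypoAware is delivered to groups by each clinic's own trainers (HypoAware). The costs counted include outpatient visits, calls, admissions and supplies (Cost-effectiveness outcomes).

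The economic result is what adoption turns on. The Abstract and the Discussion make entry into Dutch guidelines, and promotion by the national diabetes federation, conditional on proven cost-effectiveness. Intervals that are too short and acceptability curves that are too steep would feed directly into that decision.

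**Working it through.** **1. Does clinic enter the plan's own sample size?**

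Inputs from Sample size: intervention mean "0.13 (SD 0.33) 6 months post BGAT"; control mean 1.07 (SD 2.85); alpha 0.05 (two-sided reproduces the figure); power 80%; three follow-ups with correlation 0.6; ICC 0.01; four clinics per arm.

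- Difference: 1.07 − 0.13 = 0.94.
- SD: √[(2.85² + 0.33²)/2] = 2.029.
- Unclustered n per group: 2 × [2.029 × (1.960 + 0.842)/0.94]² = 73.1.
- Repeated-measures factor: (1 + 2 × 0.6)/3 = 0.733, giving 53.6.
- Design effect with 62/4 = 15.5 patients per clinic: 1 + 14.5 × 0.01 = 1.145, giving 61.4, rounded up to 62.

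This matches the stated 62 per group. Allowing for 20% loss gives 62/0.8 = 77.5 against the stated 77, a rounding difference. The plan therefore does inflate for clinic when it sets the sample size.

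**2. What would a patient-level bootstrap lose?**

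Resampling patients as independent leaves out the design effect, DE = 1 + (m − 1) × ICC. The true standard error is √DE times the patient-level one, and a nominal 95% interval covers about 2Φ(1.96/√DE) − 1. Here m runs from 15.5 (62/4, evaluable) to 19.25 (77/4, recruited; relevant because imputation can retain everyone).

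| ICC | Source | DE | SE ratio √DE | Coverage |
|---|---|---|---|---|
| 0.01 | article, primary outcome | 1.145-1.183 | 1.07-1.09 | 93% |
| 0.02 | assumed | 1.29-1.365 | 1.14-1.17 | 91-92% |
| 0.05 | assumed | 1.725-1.913 | 1.31-1.38 | 84-86% |
| 0.10 | assumed | 2.45-2.825 | 1.57-1.68 | 76-79% |

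Two simulations with skewed costs agree in direction:

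- Gamma-type costs, 16 patients per clinic, patient-level percentile bootstrap: 94% at ICC 0, 92% at 0.01, 85% at 0.05, 75% at 0.10.
- Lognormal costs (log-SD 1.2), 19 per clinic, patient-level standard error: 95%, 93%, 82% and 71% at the same ICCs.

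Together the ranges are 92-93% at 0.01, 82-86% at 0.05 and 71-79% at 0.10. The 71% comes only from the lognormal simulation. The standard-error ratio alone implies about 76% there, so it is the pessimistic end.

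**3. Would resampling whole clinics do?**

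No. In the gamma-type simulation, a plain whole-clinic percentile bootstrap with four clinics per arm covered 83-86% at every ICC tried, including zero. Neither simple reading of the bootstrap sentence gives a dependable 95% interval if costs cluster.

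**4. How wide might an honest interval be?**

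Eight clinics less two arms leaves 6 degrees of freedom. The t quantile is 2.447, and 2.447/1.96 = 1.248. Multiplied by √DE, the interval is 1.34-1.36 times as wide as the patient-level one at ICC 0.01 and 1.64-1.73 times at 0.05. At 0.01 most of the widening comes from the small number of clinics.

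**The case against.** The strongest reply is that the concern reads silence as a decision. A reader might infer that the plan ignores clinic, resamples patients and so has intervals that are too narrow. The article does not say that: it names neither the resampling unit nor the imputation model. It condenses a fuller protocol, which, with an analysis plan, would be the usual place for such details. Nothing in it rules out a clustered bootstrap, and the authors plainly know about clustering. That reply stands against any claim that the intervals are wrong. It does not remove the inconsistency. The economic section is specific about its estimator, number of replications, QALY method and displays, and clinic is the one structural element it drops after the two earlier sections include it.

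A second reply is that a ratio of mean differences is simply the definition of an ICER, and those differences could come from a mixed model. That is fair, so the ratio alone proves nothing. The conditional confounder adjustment does not fill the gap, however. Clinics are nested within arm, so clinic entered as a covariate cannot be separated from treatment. Clustering has to be handled through the variance structure or the resampling.

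A third reply is that the large effects need ICCs absent from the article. This is correct, and at 0.01 the loss is modest. Finally, one might object that severe hypoglycaemia would carry different uncertainty in the two analyses. That is weak evidence of a fault, since a mean difference and a count model would differ anyway.

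**Conclusion.** The point holds as an inconsistency that should be resolved before analysis. Clinic is carried into the sample size and the clinical model, and is absent from the economic differences, imputation and bootstrap. Overstated certainty follows if patients are resampled as independent and costs or effects cluster at all; the article leaves the first condition open. With the only documented ICC (0.01, for the primary outcome), the true standard error is about 7-9% larger than the patient-level one. The more serious losses of coverage rest on assumed cost ICCs of 0.05 and 0.10 and, at their lowest, on the assumed shape of the cost distribution. Confidence is high about the inconsistency and lower about its size.

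**What to change.** State in the economic section how clinic is handled, by one of two routes:

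1. Estimate cost and effect differences with multilevel models, or one bivariate model, with a clinic random intercept and a small-sample correction (for example t with about 6 degrees of freedom). A random intercept without the correction can still under-cover with four clinics per arm.
2. Use a two-stage bootstrap within arm, clinics and then patients, with shrinkage correction, in place of a plain patient-level or plain whole-clinic bootstrap.

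Under either route, include clinic in the imputation model and derive the ICER, the plane and the acceptability curve from the resulting estimates. Report the observed clinic ICC for costs and QALYs so that readers can judge how much it mattered.

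This changes wording and code only; no design or data-collection change is needed. The cost is wider intervals, flatter acceptability curves and a little more analysis work.

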## Discussion

Existing psycho-educational interventions aimed at reducing hypoglycaemia are effective, but demanding on the recourses of the clinics, health professionals and people with diabetes. We propose to study the costs and effects of our brief psycho-educational intervention, HypoAware, in comparison to care as usual in a cluster-randomised RCT.

A potential limitation of this study could be our relatively short follow-up period of 6 months to compare group effects. It is possible that the potential benefits of HypoAware will not yet be fully visible after 6 months, because severe hypoglycaemia occurs on average 1.0 to 1.7 times a year [18]. However, in this specific group with impaired awareness of hypoglycaemia and/or recent severe hypoglycaemia, occurrence of severe hypoglycaemia is higher than in a non-selected group of diabetes patients. To study the longer term effects, we do measure the intervention group at an additional 12 months. It would not be ethical to withhold the participants in the control group our new intervention for a year, since no other structured care is available for these patients.

Another possible limitation is that we rely on self-report of hypoglycaemia since validation of hypoglycaemic episodes, for example by means of continuous glucose monitoring technology, was not feasible. Self-reported frequency of severe hypoglycaemia for the past year (and the past week for mild hypoglycaemia) seems reliable, although an underestimation of severe hypoglycaemia seems likely in case of sub-groups with a high frequency of severe hypoglycaemia [19]. In our study, we will inquire about the previous six months in case of severe hypoglycaemia.

It is not possible to blind patients and caregivers to the randomisation due to the nature of the study; however, since both groups receive HypoAware, we can assume similar expectancies in both groups.

Overall, this study will provide valuable information about the effectiveness and cost-effectiveness of a combined group and online psycho-educational intervention to reduce and prevent episodes of severe hypoglycaemia and other hypoglycaemia-related problems in type 1 and type 2 insulin-treated diabetes patients, both from a clinical and societal perspective. Since, in the current economic climate, care has to be as effective as possible, for as little money as possible, interventions have a greater chance of being implemented if cost/benefit trade-off is favourable. Studying our intervention will also contribute to the evidence of the effect of downsizing relatively ‘intensive’ and costly interventions and complementing a group format with the Internet. This format could be applied to other interventions to improve implementation, while maintaining quality and high standards of care.

If HypoAware is proven cost-effective, it will be adopted and promoted by the Dutch Diabetes Federation as a supportive tool for managing recurrent hypoglycaemia.

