### Outcomes

All measures mentioned below will be administered at the start of the study, and 2, 4 and 6 months after inclusion through web-based questionnaires. The clinical data will be collected from the medical files by the local coordinator from each clinic. The intervention group receives an additional measurement at 12 months to analyse long-term effects over time.

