#### Primary outcome

The primary outcome is *self-reported frequency of severe hypoglycaemia* after 6 months, defined as “a hypoglycaemic event serious enough to require the help of another person”.

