#### Cost-effectiveness outcomes

The obtained EQ-5D-5 L scores [14] will be used to calculate utilities according to the Dutch tariff. For the economic evaluation, costs will be measured using the TiC-P questionnaire [15] with a recall period of 2 months. Costs that will be included are direct costs of healthcare utilization (e.g., hospital admissions, outpatient visits and calls, emergency room visits, ambulance transfers, medication and medical supply usage), costs of informal care, and indirect costs (productivity loss due to work absenteeism from paid and unpaid work). If available, Dutch guideline prices will be used to value resource use. Medication use will be valued using prices of the Royal Dutch Society for Pharmacy. Lost productivity costs will be calculated according to the friction cost approach (friction period 154 days) using the mean age and sex-specific income of the Dutch population. According to the friction cost approach a sick employee is replaced after a certain amount of time (the friction period) after which there are no lost productivity costs anymore. All costs will be adjusted to the year in which most data is collected using consumer price indices.

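### Six-month recall of severe hypoglycaemia does not fit follow-up at 2, 4 and 6 months: only the month-6 report is clean, yet the sample size counts three follow-up measurements

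*Protocol article*

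**What the plan says.** Four places in the protocol article bear on this point.

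- **Discussion**, on self-report: "In our study, we will inquire about the previous six months in case of severe hypoglycaemia". No visit is excepted.
- **Outcomes**: "All measures mentioned below will be administered at the start of the study, and 2, 4 and 6 months after inclusion through web-based questionnaires". Severe hypoglycaemia is the first measure listed after this sentence.
- **Primary outcome**: the self-reported frequency of severe hypoglycaemia, taken at 6 months.
- **Sample size**: 62 patients per group, calculated "with 3 follow-up measurements and ρ = 0.6", alpha 0.05, 80% power, and an ICC of 0.01 over 8 diabetes teams.

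Statistical analyses names a multilevel generalized linear model for counts, with clustering in patients and clinics. It does not say which reports enter or over what exposure time. By contrast, the cost questionnaire is used "with a recall period of 2 months", which matches the two-monthly schedule.

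**The concern.** A six-month look-back asked every two months does not give three separate follow-up counts. The first two contain events from before inclusion, which the intervention cannot have affected, and a single event can appear in several reports. A model that gives all three reports one common treatment effect would be pulled towards no difference. Adding the reports up, for example for the cost-effectiveness ratio, would count some events more than once. If instead only the month-6 report is analysed, these problems disappear, but so does the precision that the sample size takes from three measurements. The primary outcome and its power are at stake either way.

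**Working it through.** **1. Windows (months from inclusion, six-month look-back)**

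| Report | Window | Pre-inclusion months | Post-inclusion share |
|---|---|---|---|
| Baseline | −6 to 0 | 6 | 0 |
| Month 2 | −4 to 2 | 4 | 1/3 |
| Month 4 | −2 to 4 | 2 | 2/3 |
| Month 6 | 0 to 6 | 0 | 1 |

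Baseline shares 4 months with month 2 and 2 with month 4. Months 2 and 4 share 4 months, months 4 and 6 share 4, and months 2 and 6 share 2. Across the three follow-up reports, an event in months 0–2 appears three times, one in months 2–4 twice, and one in months 4–6 once. An event in the two months before inclusion appears twice, and also at baseline.

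**2. The plan's own figure**

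Inputs from Sample size: six-month means 0.13 (SD 0.33) and 1.07 (SD 2.85), T = 3, ρ = 0.6, ICC 0.01, four clinics per arm. Two-sided alpha is assumed.

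- Difference: 1.07 − 0.13 = 0.94
- Variance: (0.33² + 2.85²)/2 = 4.116
- One measurement, no clustering: 2 × 7.849 × 4.116 / 0.94² = 73.1 per group
- Factor for three measurements: (1 + 2 × 0.6)/3 = 0.733, giving 53.6, rounded up to 54
- Design effect with 62/4 = 15.5 per clinic: 1 + 14.5 × 0.01 = 1.145; 54 × 1.145 = 61.8, so 62

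The stated 62 per group is reproduced, and it needs the three-measurement factor. Power at 62: SE = √(2 × 4.116 × 0.733 × 1.145 / 62) = 0.334; 0.94/0.334 − 1.96 = 0.86, or 80%.

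**3. If all three reports share one treatment effect (illustration)**

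Assume a common pre-inclusion rate of (1.61 + 1.76)/2 = 1.685 per six months, constant rates after inclusion, an immediate full effect, equal weights, the plan's SD, and that the published means are six-month counts.

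- Month 2: control 1.685 × 4/6 + 1.07 × 2/6 = 1.48; intervention 1.685 × 4/6 + 0.13 × 2/6 = 1.17; difference 0.31
- Month 4: control 1.275; intervention 0.648; difference 0.63
- Month 6: difference 0.94
- Mean difference: 0.63, two thirds of 0.94
- Power at 62: 0.627/0.334 − 1.96 = −0.08, or about 47%. With ρ of 0.7 or 0.8, as overlap might produce, it is about 44% or 41%.

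**4. If only the month-6 report is used**

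- SE = √(2 × 4.116 × 1.145 / 62) = 0.390; 0.94/0.390 − 1.96 = 0.45, so power is about 67%. With 77 per group and no loss to follow-up it is about 75%.
- Size for 80%: solve n = 73.1 × [1 + (n/4 − 1) × 0.01], which gives 88.6, so 89 per group before dropout.

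**5. What baseline adjustment could return**

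The protocol does not give the correlation r between the baseline and month-6 reports, so r is an assumption here. In the linear approximation the variance is multiplied by 1 − r². At r = 0.3 the factor is 0.91, SE 0.372 and power about 71%. At r = 0.6 the factor is 0.64, SE 0.312 and power about 85%. The factor matches the plan's 0.733 at r = √(1 − 0.733) = 0.52.

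**The case against.** The strongest reply is that the primary outcome as defined is clean. It is set at 6 months, and a six-month look-back at that visit covers months 0 to 6 with no pre-inclusion time. This stands, and a reader who infers that the primary endpoint itself is biased goes beyond the document.

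The analysis section also never states an effect averaged over three visits. A repeated-measures model with its own month-6 contrast need not be diluted by two thirds. That stands too: dilution follows only from a common effect across visits, which the sample size suggests but does not establish.

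A reader might take 47% as the power of the trial. It rests on the assumptions listed in the working, and two of these are weak. The SD of 0.33 after treatment is kept for windows that are mostly pre-inclusion, although the baseline SDs are 3.49 and 3.71. The two-thirds factor is on the mean-difference scale, while a count model usually estimates a rate ratio. Higher correlation from overlap costs precision and does not by itself bias a model that allows for it. Double counting in the economic evaluation arises only if reports are summed, and the document does not say they will be.

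Finally, the recall period comes from one sentence in the Discussion, and the questionnaire may be worded differently at months 2 and 4. That is possible, but this document states only six months. It is also not mere missing detail: schedule, recall and sample size are all stated, and as stated they do not fit together.

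**Conclusion.** The point holds as an inconsistency between the stated recall, the visit schedule and the power calculation. The window conflict needs no assumption beyond reading the Outcomes and Discussion sentences as written.

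Its consequence depends on a choice the document leaves open. Using all three reports with a common effect dilutes the contrast, and the 0.63 and 47% only illustrate its size. Using the month-6 report alone is sound but gives about 67% power at 62 per group from the plan's own inputs, not 80%. Baseline adjustment may recover some or all of that gap, but only with a correlation that the plan would have to state and justify. The arithmetic behind 62 per group is not itself wrong. What fails is the premise that the three reports are three measurements of the same full effect.

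**What to change.** For data collected with six-month recall:

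1. Define the primary analysis as the month-6 report (months 0 to 6), with the baseline six-month report as covariate.
2. Exclude the month-2 and month-4 reports from the primary treatment effect and from any summed count of severe hypoglycaemia in the cost-effectiveness analysis.
3. Restate the power for one follow-up measurement: about 67% at 62 per group before any gain from baseline adjustment. If such a gain is claimed, give the assumed baseline–month-6 correlation.
4. State the recall period used at each visit, so that Outcomes, Primary outcome, Sample size and Discussion agree.

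An alternative is to ask at each visit about the time since the previous questionnaire and analyse the summed 0–6 month count with an exposure offset. It suits only participants who have not yet started follow-up. Data collection is under way, and changing the question midway would mix recall windows. A sum also needs every questionnaire answered, or an adjustment for exposure.

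The cost is a few sentences, a less favourable stated power, and the loss of the month-2 and month-4 reports from the primary analysis.
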